#### **3.5.3 DSM-5 Criteria for FSD**

FSD refers to various disturbances or impairments of sexual functioning, of which low sexual desire and sexual arousal problems are the most common among women.

In May 2013 the DSM-IV-TR was replaced by the DSM-5. Up until then a problem with sexual desire was classified as HSDD, and a problem with sexual arousal was classified as FSAD. Because of the significant overlap between arousal and desire, recommendations were done for revision of the DSM-IV-TR criteria. In the DSM-5 these two sexual problems are combined into the new female sexual interest and arousal Disorder (FSIAD).

In this study subjects with desire and/or arousal problems will be diagnosed according to the DSM-5 criteria for FSIAD. To qualify for FSIAD according to the DSM-5, three of the six indicators mentioned in criterion A should be met. For this study two of the three indicators of criterion A that should be met these are; 'absent/reduced interest in sexual activity' and 'absent/reduced sexual/erotic thoughts or fantasies'. These indicators match with the main indicators of the formerly used DSM-IV-TR diagnosis of HSDD. Because of this, all women who meet these criteria are automatically diagnosed as having HSDD (but not vice versa).

For this study, subjects may be enrolled when FSIAD (with or without female orgasmic disorder) is diagnosed by a trained health care professional.

#### Diagnostic Criteria for FSIAD

- A. Lack of, or significantly reduced, sexual interest/arousal, as manifested by at least three of the following:
  - 1. Absent/reduced interest in sexual activity
  - 2. Absent/reduced sexual erotic thoughts or fantasies
  - 3. No/reduced initiation of sexual activity, and typically unreceptive to a partner's attempts to initiate.
  - 4. Absent/reduced sexual excitement/pleasure during sexual activity in almost all or all (approximately 75%-100%) sexual encounters (in identified situational contexts of, if generalized, in all contexts).
  - 5. Absent, reduced sexual interest/arousal in response to any internal or external sexual/erotic cues (e.g., written, verbal, visual).
  - 6. Absent/reduced genital or nongenital sensations during sexual activity in almost all of all (approximately 75%-100%) sexual encounters (in identified situational contexts or, if generalized, in all contexts).
- B. The symptoms in Criterion A have persisted for a minimum duration of approximately 6 months.
- C. The symptoms in Criterion A cause clinically significant distress in the individual.
- D. The sexual dysfunction is not better explained by a nonsexual mental disorder or as consequence of severe relationship distress (e.g. partner violence) or other significant stressors and is not attributable to the effects of a substance/medication or another medical condition.

Lifelong: The disturbance had been present since the individual became sexually active.

Acquired: The disturbance began after a period of relatively normal sexual function.

Generalized: Not limited to certain types of stimulation, situations, or partners.

Situational: Only occurs with certain types of stimulation, situations, or partners.

Mild: Evidence of mild distress over the symptoms in Criterion A.

Moderate: Evidence of moderate distress over the symptoms in Criterion A.

Severe: Evidence of severe or extreme distress over the symptoms in Criterion A.

#### Diagnostic Criteria for FOD

- A. Presence of either of the following symptoms and experienced on almost all or all (approximately 75%-100%) occasions of sexual activity (in identified situational contexts or, if generalized, in all contexts):
  - 1. Marked delay in, marked infrequency of, or absence of orgasm.

2. Markedly reduced intensity of orgasmic sensations

- B. The symptoms in criterion A have persisted for a minimum duration of approximately 6 months.
- C. The symptoms in Criterion A cause clinically significant distress in the individual.
- D. The sexual dysfunction is not better explained by a nonsexual mental disorder or as a consequence of severe relationship distress (e.g., partner violence) or other significant stressors and is not attributable to the effects of a substance/medication or another medical condition.

Lifelong: The disturbance has been present since the individual became sexually active.

Acquired: The disturbance began after a period of relatively normal sexual function.

Generalized: Not limited to certain types of stimulation, situations, or partners.

Situational: Only occurs with certain types of stimulation, situations, or partners.

Specify if never experienced an orgasm under any situation

Mild: Evidence of mild distress over the symptoms in Criterion A.

Moderate: Evidence of moderate distress over the symptoms in Criterion A.

Severe: Evidence of severe or extreme distress over the symptoms in Criterion A.

### **3.5.4 Exclusion Criteria**

#### **Criteria for exclusion**

Subjects who meet *any* of the following criteria are not eligible to participate in the study:

#### Cardiovascular Conditions

- 1. Any underlying cardiovascular condition, including unstable angina pectoris, that would preclude sexual activity;
- 2. Systolic blood pressure  $\geq 140$  mmHg and/or diastolic blood pressure  $\geq 90$  mmHg (supine blood pressure). For subjects  $\geq 60$  years old and without diabetes mellitus, familial hypercholesterolemia, or cardiovascular disease: systolic blood pressure  $\geq 160$  mmHg and/or diastolic blood pressure  $\geq 90$  mmHg;
- 3. Systolic blood pressure  $\leq 90$  mmHg and/or diastolic blood pressure  $\leq 50$  mmHg (supine blood pressure);

#### Gynecological and Obstetric Conditions

- 4. Use of any contraceptive containing anti-androgens (e.g. Cyproteron acetate) or (anti)androgenic progestogens (drospirenone, dienogest, chlormadinone acetate and norgestrel);

5. Use of any contraceptive or hormone replacement therapy (HRT) containing more than 50 µg/day of estrogen;
6. Pregnancy or intention to become pregnant during this study (Note: A urine pregnancy test will be performed in all women of child bearing potential prior to the administration of study medications);
7. Lactating or delivery in the previous 6 months prior to signing Informed Consent Form;
8. History of bilateral oophorectomy;
9. Other unexplained gynecological complaints, such as clinically relevant abnormal uterine bleeding patterns;
10. Perimenopausal status (cycle shortening/irregular menstrual bleeding in the last 12 consecutive months and/or occurrence of vasomotor symptoms (e.g. hot flashes, night sweating) and/or FSH levels (>40 IU/L) for women from age 40 onwards; in women with a history of hysterectomy perimenopausality can be assessed by FSH levels (> 40 IU/L) and/or vasomotor symptoms);

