#### **3.5.2 Inclusion Criteria**

##### **Criteria for inclusion**

Subjects must meet *all* of the following criteria:

1. Provision of written informed consent;
2. Females between 18 and 70 years of age, inclusive, pre- or postmenopausal, with FSIAD (comorbidity with female orgasmic disorder [FOD]; only as secondary diagnosis) is allowed. The diagnosis of FSIAD will be established by a trained health care professional;
3. Be involved in a stable, communicative, monogamous relationship and have a sexually functional partner who will be at home for the majority of the study duration;
4. Healthy with normal medical history, physical examination, laboratory values, and vital signs; exceptions may be made if the investigator considers an abnormality to be clinically irrelevant;
5. Use of highly effective contraception.

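### Exclusion 10, read literally, can exclude postmenopausal women whom inclusion 2 admits up to age 70, because it has no exemption for women already past the menopause

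*Protocol*

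**What the plan says.** Inclusion 2, identical on this point in the synopsis and in Protocol Section 3.5.2, admits "Females between 18 and 70 years of age, inclusive, pre- or postmenopausal, with FSIAD".

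The exclusion list works by single hits: women who meet any one of its "criteria are not eligible to participate in the study". Exclusion 10, under Gynecological and Obstetric Conditions in the synopsis and in Section 3.5.4, is headed by the status and then spells it out: "Perimenopausal status (cycle shortening/irregular menstrual bleeding in the last 12 consecutive months and/or occurrence of vasomotor symptoms", followed, again joined as an alternative, by "FSH levels (>40 IU/L) for women from age 40 onwards". For women without a uterus it adds that "in women with a history of hysterectomy perimenopausality can be assessed by FSH levels (> 40 IU/L) and/or vasomotor symptoms".

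Other text shows that older and postmenopausal women are expected. Exclusion 2 sets a separate systolic limit for women aged 60 or over. Exclusion 5 bars only "Use of any contraceptive or hormone replacement therapy (HRT) containing more than 50 µg/day of estrogen", so hormone replacement up to that limit is allowed. FSH is measured at screening (Section 4.3.6.5 and Appendix 3).

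**The concern.** Inclusion 2 treats postmenopause as an admissible category. Exclusion 10 should therefore separate perimenopausal from postmenopausal women, but two of its three elements do not do so as written. A raised FSH or a hot flush counts against a woman whether her periods are becoming irregular or stopped years ago.

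Two things are at stake. The first is the population. The primary objective is to validate the demarcation formula in women with FSIAD, and Section 2.1.5.2 intends the formula for phase 3 studies and clinical use. The formula contains the androgen metabolites ADT-G and 3α-diol-G, and Section 2.1.5.1 itself names menopause and adrenal ageing as influences on androgen precursors. Menopausal status may therefore bear on the predictor under test, and a sample short of postmenopausal women would give weak support for using the formula in them. The second is consistency. Up to two sites will recruit, and a literal and a purposive reading of the criterion yield different populations. Analysis after enrolment cannot restore women who were turned away.

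**Working it through.** The protocol states no figure on this point, so the check compares the criteria and then asks whether the size can be determined.

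**Step 1: apply each element of exclusion 10 to a woman whose periods stopped several years ago.**

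| Element | Separates peri- from postmenopause? |
|---|---|
| Shortened cycles or irregular bleeding in the last 12 months | Yes. With no bleeding she does not meet it |
| Vasomotor symptoms | No. Nothing in the text ties them to the transition |
| FSH above 40 IU/L, age 40 or older | No. There is no upper age limit and no reference to time since the last period |

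The elements are joined so that any one suffices. The age qualifier may attach to FSH alone or to all three elements; either way, a woman aged 40 or older with vasomotor symptoms is caught.

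**Step 2: an example.** Take a hypothetical healthy woman of 58, six years without periods, with FSH 70 IU/L. She satisfies inclusion 2 on age and menopausal status. She also satisfies the FSH element of exclusion 10. Both criteria cannot be applied literally to give one answer.

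**Step 3: hysterectomy.** The bleeding element, the only one that discriminates, is unavailable. The two remaining tests are those that do not separate the categories.

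**Step 4: can the share excluded be found?** Let f be the proportion of postmenopausal candidates with FSH above 40 IU/L and v the proportion with vasomotor symptoms. The protocol gives neither, so both are assumptions. If they are independent, the share caught is 1 − (1 − f)(1 − v). If they overlap fully, it is max(f, v).

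| f | v | Independent | Full overlap |
|---|---|---|---|
| 0.3 | 0.1 | 1 − 0.7 × 0.9 = 37% | 30% |
| 0.4 | 0.1 | 1 − 0.6 × 0.9 = 46% | 40% |
| 0.5 | 0.1 | 1 − 0.5 × 0.9 = 55% | 50% |
| 0.7 | 0.4 | 1 − 0.3 × 0.6 = 82% | 70% |
| 0.9 | 0.6 | 1 − 0.1 × 0.4 = 96% | 90% |

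Now let a share h use permitted HRT, and assume f = v = 0.1 among them, so that 1 − 0.9 × 0.9 = 19% of users are caught. The total is (1 − h)[1 − (1 − f)(1 − v)] + 0.19h.

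| f, v in non-users | h = 0.2 | h = 0.4 |
|---|---|---|
| 0.5, 0.2 | 0.8 × 0.60 + 0.038 = 52% | 0.6 × 0.60 + 0.076 = 44% |
| 0.7, 0.3 | 0.8 × 0.79 + 0.038 = 67% | 0.6 × 0.79 + 0.076 = 55% |
| 0.9, 0.5 | 0.8 × 0.95 + 0.038 = 80% | 0.6 × 0.95 + 0.076 = 65% |

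The answer runs from 30% to 96% depending on inputs that the protocol does not supply.

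**Step 5: what is not touched.** The sample size in Section 6.1 rests on 75 against 75 women, an AUC of 0.65 against 0.5, and alpha 0.05. None of these depends on menopausal status. No hypothesis in Section 2.2 and no analysis in Section 6.3 uses menopausal status, and Section 4.2 names no menopausal factor in the randomization.

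**The case against.** The strongest reply is that the operative words are the heading of the criterion, perimenopausal status, and that the parenthesis only lists signs of it. Inclusion 2 treats postmenopausal women as a separate, welcome group, the HRT allowance fits that intention, and the hysterectomy clause is permissive in tone. A sensible investigator would enrol the 58-year-old.

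Part of this stands: the text allows that reading, so exclusion is possible rather than certain. It does not remove the defect. The parenthesis is the only working definition given, postmenopause is defined nowhere, and, unlike exclusions 14, 17, 18, 21 and 30, this criterion makes no reference to the investigator's opinion. After hysterectomy even a purposive reader is given no way to tell the groups apart. Two reasonable sites could therefore differ.

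It is also right that the harm is limited. The design has no postmenopausal stratum, and the drug effects are within-woman differences. The 150 women are those randomized; women who fail screening are never among them, so exclusion 10 changes who fills the 150 and does not subtract from it.

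**Conclusion.** The contradiction is in the current text, in both the synopsis and Section 3.5. Exclusion 10 as written can exclude postmenopausal women whom inclusion 2 admits, and it can be applied differently by different sites. It should be fixed. The consequence lies in the enrolled population and in generalisability to postmenopausal women; power, the AUC calculation and type I error are unaffected.

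A reader might infer that most postmenopausal women would be screened out and that the group would all but vanish. The protocol does not support that: it gives no distribution of FSH, symptoms or HRT use and no expected share of postmenopausal women. On assumed inputs the share caught exceeds one half over much of the range but not all of it. Nor does the protocol support an inference that the postmenopausal women who remain would be mainly HRT users, since it gives neither HRT prevalence nor any effect of permitted HRT on FSH.

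The textual finding needs none of the assumed proportions.

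**What to change.** Reconcile inclusion 2 with exclusion 10 in the synopsis and in Sections 3.5.2 and 3.5.4, by one of two routes.

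- **If postmenopausal women are wanted:** define the pre-, peri- and postmenopausal categories in the protocol. State that the FSH and vasomotor elements apply only to women who are not already postmenopausal. Give a way to separate the categories after hysterectomy. The definitions and any threshold are for the sponsor to choose.
- **If they are not wanted:** remove the reference to postmenopausal women from inclusion 2 and restrict the study's conclusion accordingly.

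On a neighbouring point, inclusion 5 ("Use of highly effective contraception") is stated for every subject, whereas the Lybrido and Lybridos parts of Section 2.3 and the Restrictions paragraph in Section 3.5.4 word the contraception requirement differently and partly for oral-contraceptive users. These passages must be reconciled too.

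The cost is a wording amendment, best made before screening starts. FSH and gynecological history are already collected at V0, so no new test is needed unless the rule chosen for women after hysterectomy calls for one. The first route gives a more heterogeneous sample than the literal criterion would, but it is the sample that inclusion 2 already describes.

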#### Other Medical Conditions

11. Liver and/or renal insufficiency (aspartate aminotransferase, alanine aminotransferase and gamma glutamyltransferase > 3 times the upper limit of normal and/or estimated glomerular filtration rate (eGFR) < 60.00 mL/min based on the Cockcroft-Gault formula);
12. Any current endocrine disease or endocrinopathy (e.g. uncontrolled thyroid function) as determined by medical history, basic physical examination and/or laboratory values significantly outside normal range of the central laboratory; or uncontrolled diabetes mellitus (HbA1c > 7.5%);
13. Free- and/or total testosterone levels outside the upper limit of the reference range of the central laboratory;
14. Any current clinically relevant neurological disease which, in the opinion of the investigator, would compromise the validity of study results or which exclude from use of sildenafil, buspirone and/or testosterone;
15. History of hormone-dependent malignancy (including all types of breast cancer);
16. Positive test result for immunodeficiency virus, hepatitis B, or hepatitis C (acute and chronic hepatitis infection);

Psychological/Psychiatric Factors

17. History of (childhood) sexual abuse that, in the opinion of the investigator, could result in negative psychological effects when testosterone is administered;
18. (Psychotherapeutic and/or pharmacological treatment for) a psychiatric disorder (other than those under inclusion criterion 6) that, in the opinion of the investigator, would compromise the validity of study results or which could be a contraindication for sildenafil, buspirone and/or testosterone use;
19. Current psychotherapeutic treatment for female sexual dysfunction;
20. Current genito-pelvic pain/ penetration disorder according to the Diagnostic and Statistical Manual of Mental Disorders, fifth edition (DSM-5);
21. A substance abuse disorder that, in the opinion of the investigator, is likely to affect the subject's ability to complete the study or precludes the subject's participation in the study;

Concomitant Medications

22. Use of potent CYP3A4 inhibitors (eg, ritonavir, ketoconazole, itraconazole clarithromycin, erythromycin and saquinavir);
23. Use of potent CYP3A4 inducers (eg, carbamazepine, phenytoin, phenobarbital, St John's wort, rifampin);
24. Use of antidepressants including SSRIs, tricyclic and other;
25. Use of any other medication that interferes with study medication (eg, triptans, monoamine oxidase [MAO] inhibitors [includes classic MAO inhibitors and linezolid] and spironolactone);
26. Use of medication (including herbs) that would compromise the validity of study results;
27. Use of testosterone therapy within 6 months before study entry prior to signing the Informed Consent Form;

General

28. Illiteracy, unwillingness, or inability to follow study procedures;
29. Participation in other clinical trials within the last 30 days;

30. Any other clinically significant abnormality or condition which, in the opinion of the investigator, might interfere with the participant's ability to provide informed consent or comply with study instructions, compromise the validity of study results, or be a contraindication for buspirone, and/or sildenafil and/or testosterone use.

#### Restrictions

Only concomitant medications which the investigator has deemed safe may be used during the study. The use of alcohol is allowed, unless contraindicated due to the use of allowed concomitant medication; excessive drinking is discouraged. There is evidence that alcohol will not induce negative side effects or negatively influence sildenafil, buspirone or testosterone. Subjects on acceptable oral contraceptives will be instructed to use highly effective contraception from the screening visit (V0) until the final follow-up visit (V6).

## 4 STUDY ACTIVITIES AND EVALUATION METHODS

### 4.1.1 Study Medication & Route of Administration

#### *Lybrido*

Lybrido is a fixed-dose combination of testosterone and sildenafil citrate. The drug product is a 9 mm, round, biconvex, white, menthol-flavored tablet for sublingual administration. The outer, polymeric, film coating contains testosterone (0.5 mg) that is released immediately after sublingual administration. The inner core of the tablet contains sildenafil (50 mg). This inner core has a polymeric coating designed to delay release of the sildenafil for approximately 2.5 hours; after this time delay, the sildenafil is released immediately (i.e., it is not a sustained release).

#### *Lybridos*

Lybridos is a fixed-dose combination of testosterone and buspirone hydrochloride. The drug product is a 9 mm, round, biconvex, white, menthol-flavored tablet for sublingual and oral administration. The outer, polymeric, film coating contains testosterone (0.5 mg) that is released immediately after sublingual administration. The inner core of the tablet contains buspirone hydrochloride (10 mg). This inner core has a polymeric coating designed to delay release of the buspirone for approximately 2.5 hours; after this time delay, the buspirone is released immediately (i.e., it is not a sustained release).

#### *Placebo*

The placebo has the exact same appearance and flavor as Lybrido and Lybridos.

#### *Dosing Instructions*

Subjects will be instructed to keep the tablet under their tongue for 90 seconds and swish the produced saliva beneath their tongues during these 90 seconds, then to swallow the tablet as a whole thereafter, without chewing or otherwise disrupting the dosage form.

A total of 8 doses will be provided for each medication regime; 8 doses Lybrido, 8 doses Lybridos, and 2x (placebo run in and placebo in the double blind regime) 8 doses placebo. Subjects are required to take a minimum of 4 doses over each 2-week treatment regime (2 dose/week). The other 4 doses may be taken as desired (i.e., "on demand") throughout the 2-week treatment regime; dosing is permitted every day until all doses are used. If within a regime a subject uses all doses, medication will not be resupplied.

### 4.1.2 Packaging, Labeling, and Storage of Study Medication

All study medications will be supplied in labeled, high density polyethylene bottles of 8 tablets, which should be stored at 25°C (77°F); temperature excursions within the range of 15°C to 30°C (59°F to 86°F) are permitted.

All study medication must be stored in a lockable area with restricted access, and a temperature log or chart must be maintained to monitor the environment.

The following information will be included on the study medication labels: protocol number, kit identification number, batch number, description of contents, dosing instructions, storage instructions, subject identification number, identification of principal investigator, and sponsor contact information.

When study medication is dispensed, prior to each medication regime, the medication will be taken from the original bottle and put in a designated bottle, fitted with a MEMSCap, by the patient. (See section 7.4. for more information on the MEMSCap system and the use of designated bottles). This will be supervised by a study physician.

#### **4.2 Enrollment and randomization**

Subjects will be enrolled after meeting the inclusion/exclusion criteria and within 12 weeks after screening (V0) (before Visit 1). Thereafter they complete a 2-week single blind placebo regime. Up until visit 2, subjects will only receive placebo (run in period). However, since all medication is packed into a single kit, subjects will be randomized prior to V1. The placebo run-in period is followed by a double blind 6-week treatment period. This treatment period consists of a 2-week Lybrido, a 2-week Lybridos, and a 2-week placebo regime. Each subject completes the treatment regime in a randomized order. The randomization schedule follows a Williams design with 6 sequences. The list with the randomized medication kit-numbers will be designed by an independent statistician. Subjects will be randomized, at least 24 hours before V1, using the electronic CRF. One of the unique medication code numbers from the randomization schedule will be coupled with the randomized subject.

A subject identification code will be used to keep the data anonymous. The code will consist of a 2-digit site code, a 4-digit subject screening number and a 3-digit randomization number (e.g., 01-0123-001). Access to the key for the code (subject identification log) will be restricted and safeguarded by the Medical Monitor. If a subject discontinues from the study, the unique subject identification code will not be used again.

In alignment with the intention-to-treat analysis, subjects who have received study medication will not be replaced. A subject will be replaced if she has not yet received any study medication (e.g., the subject decides to stop before V1) but only during the enrolment period (a duration of 16 weeks) of the study. When the enrolment period has ceased, subjects will not be enrolled or replaced.

